#### Follow-up (timepoint 2 (T2))

The data from the children monitored by the WheezeScan are reviewed 2 weeks after the baseline visit. WheezeScan and e-diary data are analysed and used for reclassification of the ‘asthma’ diagnosis (Dx-T2). The ‘definite yes’ and ‘possible’ groups following the second reclassification step then commence, when considered clinically appropriate, 4 weeks of inhaled corticosteroid (fluticasone 100 µg two times per day, using a spacer±mask). The ‘definite no’ group continues in the study using the WheezeScan and administering 400 µg of inhaled SABA (using a spacer±mask) if wheeze is detected and then reapplying the WheezeScan 10 min later to determine and record whether RAO is present. As above, the SABA and WheezeScan steps may be repeated once. Also, at T2, PROs are collected.

#### Final visit (timepoint 3 (T3))

6 weeks post-T1, the children are then again reclassified using WheezeScan data and response to inhaled corticosteroids, the latter if used following T2 (Dx-T3). Also, at T3, PROs and economic data from all study participants are collected.

At the end of the study, a second independent respiratory specialist reviews clinical data, including available FeNO results and WheezeScan data, from all participating children and based on this information classifies the asthma diagnosis in the child (labelled as the independent classification [i-]). The independent person is blinded to the treating clinician’s assessment.

In addition, parents/caregivers of those who used the WheezeScan are also asked to give feedback on the usefulness of the device, using a Likert scale question. The question, framed with advice from our consumer’s group, is as follows: ‘The WheezeScan is useful in managing my child’s wheezing problems?’ The Likert scale ranges from 1 (strongly disagree) to 5 (strongly agree).

Study exit criteria are: consent withdrawn or intolerance of SABA or inhaled corticosteroids (as determined by study site doctors or treating clinicians).

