## Aims and hypotheses

Our primary aim is to determine in preschool children (aged 0.5–6 years) suspected of asthma whether adding WheezeScan to routine clinical assessment (vs assessment without WheezeScan) improves the diagnosis of asthma. Our primary hypothesis is that using WheezeScan in preschool children suspected of asthma is associated with increased definitive asthma diagnoses in this age group.

Our secondary aims are to examine the effect of using WheezeScan on: (a) PROs and (b) healthcare costs. Our secondary hypothesis is that using WheezeScan in preschool children suspected of asthma is associated with improved QoL without incurring additional healthcare costs.

Additionally, we aim to evaluate the perceived usefulness of WheezeScan for parents/caregivers using a qualitative evaluation.

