## Methods and analysis

### Design

We are undertaking a prospective multicentre cohort study. Recruitment commenced from 1 February 2024 and is continiuing.

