### Outcomes and endpoints

Asthma classificationsAt T1, asthma classification is defined by the treating specialist clinician using clinical parameters.For other timepoints (T2 and T3).‘Definite yes’= presence of RAO defined by disappearance of wheeze using WheezeScan after 400 µg of inhaled SABA.‘Definite no’= no wheeze documented.‘Possible’=wheeze without clear response post-SABA or does not fit into the definite ‘yes’ or ‘no’ category.Independent classification by a second specialist after reviewing the data at T3.‘i-Asthma’= resolution of symptoms with treatment using WheezeScan data supported by FeNO >25ppb (if available).^11^‘i-no’= no effect of treatment.‘i-possible’= neither ‘yes’ nor ‘no’.Agreement between clinician and WheezeScan detection of wheeze at T1.PROs (PedsQL,^28^ PC-QoL^29^ (if chronic cough present)).Healthcare resource use and costs (healthcare system and family perspectives).Likert scale question relating to usefulness of WheezeScan at T3.See online supplemental file 1 for further description.

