### Endpoints

#### Primary

Proportion of children with a definite diagnosis (yes/no) of asthma from T3 to T1, based on the classification provided by the treating specialist clinician.

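### The T3 asthma classification has two different rules, and if steroid response is used the T1-T3 change cannot be attributed to WheezeScan alone

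*Protocol article*

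**What the plan says.** All references are to the protocol article.

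- **Aim** (Aims and hypotheses): to find out "whether adding WheezeScan to routine clinical assessment (vs assessment without WheezeScan) improves the diagnosis of asthma".
- **Design:** "We are undertaking a prospective multicentre cohort study". There is no concurrent control group.
- **Primary endpoint:** "Proportion of children with a definite diagnosis (yes/no) of asthma from T3 to T1, based on the classification provided by the treating specialist clinician". The Analyses section compares the proportions by McNemar's test.
- **T1** (Outcomes and endpoints): "asthma classification is defined by the treating specialist clinician using clinical parameters".
- **T2** (Follow-up): "WheezeScan and e-diary data are analysed and used for reclassification of the" diagnosis. After this step, children classed 'definite yes' or 'possible' may start four weeks of ICS where the clinician judges it appropriate.
- **T3, visit text** (Final visit): "the children are then again reclassified using WheezeScan data and response to inhaled corticosteroids, the latter if used following T2 (Dx-T3").
- **T2 and T3, outcome definitions** (Outcomes and endpoints): 'definite yes' is "presence of RAO defined by disappearance of wheeze using WheezeScan after" inhaled short-acting β2-agonist (SABA). 'Definite no' means that no wheeze was recorded. 'Possible' is wheeze that does not clearly respond to SABA, or anything else. ICS response does not appear.
- **Abstract** (Methods and analysis): the endpoint is the treating clinician's assessment using WheezeScan data. ICS response is not mentioned here either.

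**The concern.** The two descriptions of T3 use different information, and both concern the classification that feeds the primary test. If sites or clinicians follow different texts, the same child can be counted differently.

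The second issue is what the difference means. The aim is a comparison with and without WheezeScan, but the data are T1 against T3 in the same children. Under the visit text, response to a treatment trial can inform the T3 diagnosis and cannot inform the T1 diagnosis. By T3 there have also been six weeks of observation, an e-diary, weekly parent contact and an optional repeat clinical assessment. A rise in definite diagnoses could be reported as the yield of the device when part of it came from these other sources.

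**Working it through.** **1. The plan's own figure.** Inputs from Sample size estimates: 15% at T1, 30% at T3, correlation 0.25, n = 102, power above 80%. Alpha is not given there; I assume 0.05 two-sided.

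- Both positive: p11 = 0.15×0.30 + 0.25×√(0.15×0.85×0.30×0.70) = 0.0859.
- Discordant cells: 0.15 − 0.0859 = 0.0641 and 0.30 − 0.0859 = 0.2141. Their sum is pd = 0.2782 and their difference is d = 0.15.
- McNemar: n = [1.96√pd + 0.8416√(pd − d²)]²/d² = 94.6, so 95.
- With continuity correction, (n/4)[1 + √(1 + 2/(nd))]² = 101.2, so 102.

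The sample size reproduces. The issue is what the difference measures.

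**2. One child under each T3 text.** Suppose that the child wheezes without clear SABA response before T2, is 'possible' at T2, starts ICS, and has no wheeze recorded afterwards.

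| T3 text | Wheeze window | T3 class | Counts as definite (yes or no)? | Counts as definite yes? |
|---|---|---|---|---|
| Final visit | not stated | could be asthma, as an ICS responder | yes | yes |
| Outcome definitions | all six weeks | possible | no | no |
| Outcome definitions | T2 to T3 only | definite no | yes | no |

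The same records give three classes. The window matters by itself: a child with SABA reversal before T2 and no wheeze on ICS is 'definite yes' over six weeks but 'definite no' if only T2 to T3 counts. The available recordings are also unclear. The abstract describes six weeks of home use, whereas the T2 section describes continued use only for the 'definite no' group. Children who are 'definite yes' at T1 are not among those taught home use.

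**3. What differs between T1 and T3.** WheezeScan data enter the classification, ICS response may enter it, and observation is longer. Only the first is named in the aim. No reading at the same time without WheezeScan separates them.

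**4. What the test can see.** The article does not give the rise that would occur without any device effect, so the rises below are assumptions. Take T1 = 15%, T3 = 15% + x, correlation 0.25, n = 102, with x due entirely to ICS response and follow-up. Cells follow as in step 1; for x = 10 points they are 0.0738 and 0.1738. Enumerating the discordant pairs gives the chance of a significant result (exact test to uncorrected asymptotic test):

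| Assumed non-device rise | P(significant) |
|---|---|
| 0 points | 2.9% to 5.2% |
| 5 points | 13.5% to 19.7% |
| 7.5 points | 27.3% to 36.1% |
| 10 points | 45.2% to 55.1% |
| 15 points | 79.3% to 85.5% |

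This shows only that McNemar's test responds to a rise whatever its source. It does not estimate the bias. It also borrows the 15% and 30% for children diagnosed with asthma, whereas the endpoint is worded as a definite yes or no.

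**The case against.** The strongest reply is that the visit text lists the information reviewed and the outcome section sets the categories. The abstract agrees with the outcome section, and Potential study limitations says that reversibility is defined solely by resolution of wheeze after SABA. The outcome section also refers to a supplement, not shown here, that may settle the rule. This is a reasonable way to reconcile the texts, but the article does not state it: the visit text names ICS response as a basis for reclassifying, not as background. The window stays open in the article either way.

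On attribution, the limitations section concedes a risk of bias from the non-randomised design, and the hypothesis speaks of association. Extended home recording is also partly how the device is meant to help, since the Discussion argues that a clinic assessment of minutes misses the child's state over days and weeks. So not all of the six weeks is a nuisance. These points stand and limit the concern. The general caveat does not, however, name ICS response or longer follow-up.

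A reader might infer that a significant rise is to be expected even if WheezeScan adds nothing. The documents do not support that. Under the outcome definitions ICS response cannot produce a 'definite yes', and wheeze suppressed by ICS may push a child towards 'definite no', so the direction is unclear. The survey finding that response to treatment is the favoured diagnostic method is background, not a study rule. Nor is T1 strictly device-free: WheezeScan is applied to every child at baseline, although the T1 classification is said to rest on clinical parameters.

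**Conclusion.** The concern holds in two parts. First, the final-visit section contradicts the outcome definitions and the abstract on how Dx-T3 is made, and no window is given; the choice changes who counts in the primary endpoint. This follows from the text alone. Second, if ICS response is used, it enters only the T3 side, and the T1-T3 change reflects WheezeScan, a treatment trial and longer follow-up together. It cannot be attributed to WheezeScan alone, and the general bias caveat does not cover this.

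The size cannot be derived, because the article states neither the share given ICS nor the change expected without the device. The percentages in the working rest on assumed rises.

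It would go too far to say that the T1-T3 comparison is worthless or must be replaced. It remains a valid description of change under the whole pathway, and the study is registered and recruiting.

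**What to change.** 1. Reconcile the abstract, the final-visit section and the outcome definitions so that one Dx-T3 rule and one recording window apply to the primary endpoint. Say what is used for children who are 'definite yes' at T1. Record ICS response as a separate variable.
2. Add a prespecified supporting McNemar comparison of T1 with Dx-T2, which uses WheezeScan and e-diary data before any study ICS and is already collected. State a rule for T1 'definite yes' children, who are not seen at T2 (about 0.15×102 ≈ 15 under the planning rate), for example carrying T1 forward. Carrying forward has a consequence: if only 'definite yes' counts, no child can move downwards, and six upward moves alone give an exact p of 2×0.5⁶ = 0.031. The comparison should therefore be coded as definite (yes or no) against possible, and the discordant counts reported.
3. Word the primary conclusion as a before-after change under the whole pathway: WheezeScan, follow-up and any ICS trial.

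The cost is wording in the protocol and analysis plan plus one extra analysis; no treatment or visit changes. The downside is that T2 has only two weeks of recordings, so fewer children will be reclassified, and T1 against T2 is still uncontrolled. A read by the independent specialist with WheezeScan withheld is optional only, because ICS given after T2 already reflects WheezeScan results.

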Despite the importance of detecting wheeze, there are high levels of disagreement (>50%) between parental and physician reporting of wheeze.^15^ This may cause underdiagnosis or overdiagnosis of asthma and lead to overuse or underuse of medications, children undergoing unnecessary procedures and high parental anxiety.^16 17^ Crucially, failing to recognise wheeze can delay diagnosis, especially if wheeze is recurrent, as it can defer appropriate treatment, which may lead to ongoing exacerbations, doctor visits, hospitalisations and an increased burden on parents/caregivers. In contrast, early recognition and treatment of asthma improves symptoms and quality of life (QoL).^10^,^12^

While detecting wheeze and its reversibility with SABA is not the sole predictor in the diagnostic journey for asthma in preschool children, it is still a crucial step. Addressing the poor reliability of detecting wheeze in young children^15 18^ is a clear clinical gap. Recently, this gap was highlighted by the European Respiratory Society (ERS) Taskforce statement on preschool wheezing disorders.^5^ Its importance is even greater in settings where reporting of respiratory symptoms is more challenging, such as in disadvantaged First Nations communities^19^ and in settings where there are diverse cultures and languages spoken.^18^

Reliable and objective detection of wheeze using digital technology in clinics during face-to-face visits and at home when applied by parents could lead to improved diagnosis from detecting wheeze that responds to asthma treatments. There are now clinically validated tools that can objectively define wheeze. One such tool is the WheezeScan (figure 1, Omron Healthcare, Japan), which is the world’s first clinically validated device^20^ that uses artificial intelligence to detect and differentiate wheeze from other breath sounds in young children aged 4 months to 7 years.^21^ For our study, we chose WheezeScan as its design is user-friendly, ergonomic, light and portable, allowing parents to have it with them at all times and to remove any uncertainty when breathing distress occurs. In a pilot study from Germany involving 20 children, parents detected wheeze in 22/708 (3.1%) routine two times per day recordings, but WheezeScan indicated wheeze was present in 140/708 (19.8%) of the recordings.^20^

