#### Secondary

Concordance of the asthma classification between the treating and independent specialist clinicians.Agreement between the clinical and WheezeScan detection of wheeze.Difference in PROs between the timepoints (T3−T1, T3−T2); subanalysed in accordance with whether inhaled corticosteroids were used.Composite measure of the ‘usefulness of WheezeScan’. We will consider WheezeScan clinically useful if: (a) WheezeScan assisted in a definite diagnosis (yes/no) or (b) PRO outcomes are superior in the WheezeScan-based versus independent asthma classification groups and (c) did not incur (net) healthcare costs during the study period.Healthcare resource use among the various classified groups (primary horizon at T3).

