### Data monitoring, management and analyses

Database management is based in Brisbane, as with our previous/current multicentre studies,^23^,^2530^ and is also GCP adherent. Study data are stored and managed using REDCap electronic capture tools hosted at the Queensland University of Technology server, with an additional layer of security provided by multifactor authentication. Missing data will not be imputed. A detailed statistical analysis plan will be developed prior to the analyses. This includes adjusting for potential biases (eg, age), if necessary.

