#### Analyses

For the primary aim we will compare the proportions using McNemar’s test.

For the secondary aims:

Concordance of asthma classification (definite yes, definite no, possible) between the treating clinician and the independent specialist will be undertaken using weighted Kappa. Likewise, concordance between clinician and WheezeScan detected wheeze will be undertaken using Cohen’s Kappa.Change in PROs scores will be presented as means and SD and assessed by paired t-tests (assuming normal distribution) and the proportions with scores above the minimal clinically important difference (MCID) for each PRO in each group defined at T3 compared with T1.Composite measure of ‘usefulness of WheezeScan’ will be described and presented as numbers and percentages.Healthcare resource use associated with respiratory healthcare will be costed using actual costs (when known) or market rates from the perspectives of the healthcare system provider and families for each pathway (figure 2). Uncertainty estimates will be generated using bootstrap resampling (10 000 replications).

We anticipate reporting the last two secondary aims in a separate paper, as there will be a delay in the healthcare resource use analysis.

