#### Sample size estimates

Our sample size is 102 children. This is based on conservative estimates of 15% being diagnosed with asthma at T1 and 30% at T3, with a correlation between the paired observations of 25%, which provides power>80% to detect a difference of 15% between the proportions. We will replace children with incomplete data and thus we expect to have complete data from 102 children. We conservatively estimate that 33% of children in our target group (preschool children with recurrent wheeze) have asthma (defined as RAO) and when adequately treated will be two times as likely to have significantly improved PRO above their MCID compared with when not treated due to wheeze misclassification known to be >50% in this age group.^15^

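### Drug intolerance is a reason to leave the study and incomplete cases are replaced, so the primary comparison and the usefulness composite would describe mainly children who tolerated treatment

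*Protocol article*

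**What the plan says.** Four rules in the protocol article bear on this point.

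- **Exit** (Final visit (T3)): "Study exit criteria are: consent withdrawn or intolerance of SABA or inhaled corticosteroids (as determined by study site doctors or treating clinicians". Drug intolerance stands beside withdrawn consent as a reason to leave the study, not only to stop the drug.
- **Replacement** (Sample size estimates): "We will replace children with incomplete data and thus we expect to have complete data from 102 children".
- **Missing data** (Data monitoring, management and analyses): "Missing data will not be imputed".
- **Usefulness composite** (Endpoints, Secondary): "We will consider WheezeScan clinically useful if: (a) WheezeScan assisted in a definite diagnosis (yes/no) or (b) PRO outcomes are superior" in one set of classification groups against another, "and (c) did not incur (net) healthcare costs during the study period". The and/or order is not bracketed.

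The outcomes listed are asthma classification, agreement on wheeze at T1, patient-reported outcomes (PROs), resource use and costs, and a Likert item. None counts intolerance or SABA exposure. Steroid use enters only as a subanalysis of PRO change.

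The device prompts treatment. In the baseline and T2 sections, a detected wheeze leads to inhaled SABA, which may be repeated once. A 'definite yes' or 'possible' label at T2 leads to inhaled steroid where the clinician judges it suitable.

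**The concern.** Adding the device means adding treatment decisions, so children who do badly on the resulting treatment belong in any judgement of its value. The exit rule takes them out before T3, and the replacement rule puts another child in their place. The completed 102 are then selected partly on tolerance, an event that occurs after enrolment and can follow from a device reading.

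Two results are affected. The primary McNemar comparison needs a classification at both T1 and T3. The composite draws on PRO changes that need T3 values and on economic data collected at T3. Neither would include a child who exited earlier, and the composite has no term through which the loss would show.

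**Working it through.** **1. The plan's own power figure.** Inputs from Sample size estimates: 15% at T1, 30% at T3, correlation 0.25, n = 102. Two-sided alpha of 0.05 is assumed, as the article does not state it.

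- Both positive: 0.15 × 0.30 + 0.25 × √(0.15 × 0.85 × 0.30 × 0.70) = 0.0859
- Discordant cells: 0.30 − 0.0859 = 0.2141 and 0.15 − 0.0859 = 0.0641; total 0.2782
- Power = Φ[(0.15 × √102 − 1.96 × √0.2782) / √(0.2782 − 0.15²)] = 82.9%

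The stated power above 80% is reproduced with the asymptotic test (the exact test gives 79.3%). If exits were neither followed nor replaced, asymptotic power would be 81.0% at n = 97, 78.8% at 92 and 74.0% at 82. Replacement avoids that loss. It does not make the 102 represent everyone enrolled.

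**2. What replacement hides.** The exit rates are assumptions, because the article gives none. Enrolled = 102 / (1 − rate), rounded up. The planned net change among completers is 0.15 × 102 = 15.3 children. With k children removed, the difference over all enrolled is 15.3 / enrolled if they are counted as unchanged. The extremes, with all k moving the same way, are (15.3 − k) / enrolled and (15.3 + k) / enrolled.

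| Assumed exit rate | Enrolled | Removed (k) | Counted as unchanged | Extremes |
|---|---|---|---|---|
| 2% | 105 | 3 | 15.3/105 = 14.6 points | 11.7 to 17.4 |
| 5% | 108 | 6 | 15.3/108 = 14.2 points | 8.6 to 19.7 |
| 10% | 114 | 12 | 15.3/114 = 13.4 points | 2.9 to 23.9 |

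The extremes are bounds, not forecasts. The direction of any bias is not known.

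**3. The three limbs of the composite.**

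- Limb (a), a definite diagnosis: a child who exits after T2 may have a T2 label but would still be replaced for incomplete data.
- Limb (b), PROs: the listed differences are T3 − T1 and T3 − T2, so both need T3.
- Limb (c), cost: economic data are collected at T3, and the Analyses section limits the scope: "Healthcare resource use associated with respiratory healthcare will be costed using actual costs (when known) or market rates". Care for a drug reaction not classed as respiratory need not enter.
- If the rule means (a) or [(b) and (c)], limb (a) alone suffices. If it means [(a) or (b)] and (c), cost must also pass. Neither reading contains a harm or exposure term.

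**4. Exposure, for illustration only.** The Introduction reports a pilot of 20 children in which "WheezeScan indicated wheeze was present in 140/708 (19.8%) of the recordings", against 22/708 detected by parents. The ratio is 140/22 = 6.4.

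| Basis | Routine readings | Device-detected | Parent-detected |
|---|---|---|---|
| Baseline section, 2 weeks | 2 × 14 = 28 | 28 × 140/708 = 5.5 | 28 × 22/708 = 0.9 |
| Abstract, 6 weeks | 2 × 42 = 84 | 84 × 140/708 = 16.6 | 84 × 22/708 = 2.6 |

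These are occasions per child using the device at home, if pilot rates carry over and every positive reading is treated. Children classed 'definite yes' at T1 are not among those trained for home use. The sections disagree on duration: the Abstract gives 6 weeks, the baseline section gives 2, and the T2 section states continuation only for the 'definite no' group.

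**The case against.** The strongest reply is that this is a condensed article. Adverse-event recording and follow-up after exit commonly sit in the full protocol, and the outcomes are described further in a supplement that is not shown. That stands: the lack of a safety section or a general safety endpoint here is not a defect, and nothing in the article says that exits will go unreported. The composite is also one secondary item, to be described as counts and percentages in a separate paper; it is not a test.

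A reader might draw three stronger conclusions, none of which the document supports.

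- *That harm cannot be seen.* Weekly parent contacts, health surveillance questions at T2 and T3, and the e-diary can all record problems and SABA use while a child remains in the study.
- *That the device alone triggers steroids.* They start only on a clinician's judgement.
- *That this is the main risk of the device.* The article gives no intolerance rate, and more frequent detection may be real wheeze and a benefit.

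The exposure figures are also weak as a measure of excess treatment. The 3.1% is parental detection at routine recordings, not SABA use without the device, and readings prompted by suspicion are left out.

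The reply does not reach the stated rules on exit, replacement and imputation. Together they determine who is in the analysed 102.

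**Conclusion.** The point holds in a limited form. As written, a child who does not tolerate SABA or inhaled steroid leaves the study, is replaced if data are incomplete, and is missing from the primary comparison and from the T3-based parts of the composite. Those results would describe mainly children who tolerated treatment.

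The size is unknown because no intolerance rate is given. At assumed rates of 2% to 10%, 3 to 12 children would be removed. Counted as unchanged, they would lower the planned 15-point difference by 0.4 to 1.6 points, with much wider extremes at 10%. This rests on one inference: that a child who exits before T3 counts as having incomplete data. The exposure figures (5.5 versus 0.9, or 16.6 versus 2.6) are context and do not measure harm.

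**What to change.** - Reword the exit rule so that stopping a study drug and leaving the study are separate events. The drug decision stays with clinicians.
- Unless consent is withdrawn, keep these children on the existing weekly contacts and assess them at T3. Count them in the denominator and do not replace them.
- Report the number of intolerance exits, and the SABA and steroid exposure already recorded, for all enrolled children (including any already replaced) beside any statement that the device is useful.
- Bracket the and/or rule in the composite.
- Reconcile the duration of home device use across the Abstract, the baseline section and the T2 section.

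The cost is one amendment and some added reporting, using contacts and a diary that already exist. Children kept to T3 add to the complete pairs, so power need not suffer. The usefulness result may look slightly less favourable. The article describes recruitment as continuing, and T3 data on children who exit cannot be recovered later, so the change is best made early.
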